### Statistical analysis

Efficacy: two-group comparison of the psychosocial functioning/coping with demands of daily living (SIS, MINI-ICF-P), specified affective symptomatology including mood swings (HAMD, YMRS, EPI*bipolar*, BPSS-P) and difference in perception of, reaction to and coping with stress (ABF, TICS, SRS, UBV, FERUS) at 7, 14, 24, 52 and 78 weeks with baseline values as covariates. In all cases, the 14-week value is the primary time-point of interest. A repeated measures analysis will be carried out as a secondary result.

Description of the primary efficacy analysis: ANCOVA with SIS at 14 weeks and separately with specified affective symptomatology at 14 weeks as dependent variable and baseline SIS, affective symptomatology, centre, age, sex, education and group as covariates. We will also look into influence of the therapist on results by additionally including that variable, if not highly correlated with the variable centre, into the ANCOVA. Population: intention-to-treat (ITT) analysis with last observation carried forward (LOCF) in case of missing values.

Secondary endpoints:

• Difference between the groups in MINI-ICF-P at 7, 14, 24, 52 and 78 weeks with baseline values as covariates

• Change in specified affective symptomatology including mood swings at 7, 24, 52 and 78 weeks compared to baseline within each group

• Difference between the groups in perception of, reaction to and coping with stress at 7, 14, 24, 52 and 78 weeks with baseline values as covariates

• Difference between the groups in SIS at 7, 24, 52 and 78 weeks with baseline values as covariates

• Difference between the groups in rates of developing bipolar disorders at 52 and 78 weeks

Safety: assessment of frequency and type of unwanted effects at 7, 14, 24, 52 and 78 weeks compared to baseline within the groups and difference between the groups.

The study was approved by the respective ethics committees of all participating study centres (see Table 2).

**Table 2 T2:** Ethics committees of the participating study centres

**Ethics committee**	**Reference number**
Medizinische Fakultät, TU Dresden	EK 60022010
Medizinische Fakultät, Ruhr University Bochum	3757-10
Ärztekammer Hamburg	MC-196/10
Medizinische Fakultät, Ruhr University Bochum	3782-10
Medizinische Fakultät der Universität zu Köln	10-164
Medizinische Fakultät, University Würzburg	204/12_z
Ethikkommission der Charité Berlin	EA1/233/12

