**Methods/Design:**

EarlyCBT is a randomised controlled multi-centre clinical trial to evaluate the efficacy and safety of early specific CBT, including stress management and problem solving strategies, with elements of mindfulness-based therapy (MBT) versus unstructured group meetings for 14 weeks each and follow-up until week 78. Participants are recruited at seven university hospitals throughout Germany, which provide in- and outpatient care (including early recognition centres) for psychiatric patients. Subjects at high risk must be 15 to 30 years old and meet the combination of specified affective symptomatology, reduction of psychosocial functioning, and family history for (schizo)affective disorders. Primary efficacy endpoints are differences in psychosocial functioning and defined affective symptomatology at 14 weeks between groups. Secondary endpoints include the above mentioned endpoints at 7, 24, 52 and 78 weeks and the change within groups compared to baseline; perception of, reaction to and coping with stress; and conversion to full BD.

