### Outcome measures

Primary efficacy endpoints:

• Psychosocial functioning/coping with demands of daily living (SIS) at 14 weeks

• Specified affective symptomatology (Hamilton Rating Scale for Depression (HAMD, [37]), Young Mania Rating Scale (YMRS, [38]), EPI*bipolar*, BPSS) at 14 weeks

Key secondary endpoints:

• SIS at 7, 24, 52 and 78 weeks

• Mini version of the International Classification of Functioning, Disability and Health for Mental Disorders (MINI-ICF-P, [39,40]) at 7, 14, 24, 52 and 78 weeks

• Specified affective symptomatology (HAMD, YMRS, EPI*bipolar*, BPSS) at 7, 24, 52 and 78 weeks

• Perception of, reaction to and coping with stress: Alltags-Belastungs-Fragebogen (ABF, [41]), Trierer Inventar zum chronischen Stress (TICS, [42]), Stress-Reaktivitäts-Skala (SRS, [43]), Fragebogen zum Umgang mit Belastungen im Verlauf (UBV, [44]), Fragebogen zur Erfassung von Ressourcen und Selbstmanagementfähigkeiten (FERUS, [45]) at 7, 14, 24, 52 and 78 weeks

• Development of bipolar disorders at 52 and 78 weeks (SCID).

Assessment of safety: structured assessment of adverse events (GCP standard, interview: description of type, severity and relation to intervention). See Table 1 for an overview of instruments applied.

**Table 1 T1:** Instruments applied at individual study visits

** Time**	**Baseline**	**FU 1**	**FU 2**	**FU 3**	**FU 4**	**FU 5**
**Instruments**	**Wk -1**	**Wk 7**	**Wk 14**	**Wk 24**	**Wk 52**	**Wk 78**
SIS	X	X	X	X	X	X
MINI-ICF-P	X	X	X	X	X	X
HAMD	X	X	X	X	X	X
YMRS	X	X	X	X	X	X
EPI*bipolar*	X	X	X	X	X	X
BPSS	X	X	X	X	X	X
ABF	X	X	X	X	X	X
TICS	X	X	X	X	X	X
SRS	X	X	X	X	X	X
UBV	X	X	X	X	X	X
FERUS	X	X	X	X	X	X
SCID	X				X	X

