Legend: FU, follow-up; Wk, week; SIS, Social Interview Schedule, English version: [32], German version: [33]); MINI-ICF-P, Mini version of the International Classification of Functioning, Disability and Health for Mental Disorders, [39,40]; HAMD, Hamilton Depression Symptom Scale 17 item version, [37]; YMRS, Young Mania Rating Scale, [38]; EPI*bipolar*, Early Phase Inventory for bipolar disorders, ©[name] and [name] 2010, [19]; BPSS, Bipolar Prodrome Symptom Scale-Prospective, ©[name] 2007, [20]; ABF, Alltags-Belastungs-Fragebogen, [41]; TICS, Trierer Inventar zum chronischen Stress, [42]; SRS, Stress-Reaktivitäts-Skala, [43]; UBV, Fragebogen zum Umgang mit Belastungen im Verlauf, [44]; FERUS, Fragebogen zur Erfassung von Ressourcen und Selbstmanagementfähigkeiten, [45]; SCID, Structured Clinical Interview for DSM-IV Disorders, in German: [34]. The baseline time is week minus 1.

Rationale for choosing the presented outcome measures are as follows. We chose coping with demands of daily living as one primary outcome measure as it is a sensitive measure of changes in psychosocial functioning that in turn highly influences the long-term outcome of the disorder. Our study population consists of subjects at high risk for developing BD; they do not fulfill the diagnosis (yet) but already show impairment of psychosocial functioning. Improving this should have a great impact on the course of the disease development either by postponing/alleviating or even preventing the full-blown disorder. Additionally, we use the change in affective symptomatology as a primary endpoint since psychosocial functioning is only in part explained by psychiatric symptomatology.

To get an idea about adherence on the therapist’s part to the treatment manual or instructions regarding the control group setting, videotaped treatment sessions which have been developed based on the German adapted version of the Cognitive Therapy Scale for Psychosis [46] by Wittorf *et al*. [47], will be reviewed. Adherence on the subject’s part is assessed by checking on participation in the sessions as well as home work completion in the active intervention groups.

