### Power

Sample size for the ANCOVA will be approximated with the two-sided unpaired *t*-test. The primary outcome measure is the difference in the adapted overall social maladjustment score. Here, the number of items in the categories M and S with a rating of 2, 3 or 4 is divided by the number of applicable items in the categories M and S. With an estimated effect size of about 0.5, a sample size of 2 times 50 patients is required to show this difference with a power of 80% and an alpha of 5% (calculated with G*Power 3.1.2).

We assume that the compliance will be relatively good here since the intervention does not result in major side effects and the subjects already experience symptoms. However, we assume conservatively that there will be about a 30% drop-out rate, an estimate that was accounted for in the sample size estimation. Follow-up of subjects that drop out of the study will last for the planned duration of the study.

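### The power section names one primary outcome and gives it the full 5%; the rest of the protocol names two, tested separately, with no stated rule for success

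*Protocol article*

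**What the plan says.** Four places in the protocol article treat the trial as having two primary endpoints:

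- The Methods/Design paragraph of the abstract: "Primary efficacy endpoints are differences in psychosocial functioning and defined affective symptomatology at 14 weeks between groups".
- The list under Outcome measures. Its first entry is "Psychosocial functioning/coping with demands of daily living (SIS) at 14 weeks". Its second begins "Specified affective symptomatology (Hamilton Rating Scale for Depression (HAMD, [37]), Young Mania Rating Scale (YMRS, [38" and goes on to EPIbipolar and BPSS, also at week 14.
- The rationale in the same section: "We chose coping with demands of daily living as one primary outcome measure", followed by "Additionally, we use the change in affective symptomatology as a primary endpoint".
- Statistical analysis, where the primary efficacy analysis is "ANCOVA with SIS at 14 weeks and separately with specified affective symptomatology at 14 weeks as dependent variable".

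The Power section differs: "The primary outcome measure is the difference in the adapted overall social maladjustment score". It sizes the trial on that score alone, using a two-sided unpaired t-test, an effect size of about 0.5, 80% power and an alpha of 5%, and arrives at 2 x 50 patients.

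The hypotheses under Objectives/hypotheses and at the start of the Discussion join psychosocial functioning and affective symptoms with 'and'. Neither says whether one or both must be shown.

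**The concern.** The number of primary endpoints and the condition for success fix what the 5% and the 80% refer to. The article gives one primary in one place and two in the others. The second is a domain covered by four scales, not a single defined variable.

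If SIS showed nothing and one affective scale reached p < 0.05, the Statistical analysis section would let this be reported as a primary result, while the Power section would not. The readings have different consequences:

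- If either endpoint suffices, the type I error is above 5%.
- If both are required, the power is below 80%.
- Only if SIS is the sole primary do the stated alpha and the sample-size basis refer to the same test.

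**Working it through.** **Inputs from the Power section.** d = 0.5, two-sided alpha 0.05, power 80%, 50 per arm.

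**Assumed, not in the document.** The correlation r between test statistics, and d = 0.5 on the affective variable as well (the article gives an effect size only for SIS).

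**1. The plan's own figure.**
- n per arm = 2(z₀.₉₇₅ + z₀.₈₀)²/d² = 2(1.960 + 0.842)²/0.25 ≈ 62.8, so 63 per arm, or 64 with the t distribution. The stated 50 is not reproduced.
- Power of one two-sided t-test at d = 0.5 with 50 per arm is 69.7%.
- A one-sided 5% test would need 50 per arm (normal) or 51 (t).

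This is a separate problem from the number of primaries. It matters here only because it enters step 4.

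**2. Either endpoint suffices, two tests at 5% each, no true effect.**
- Independent: 1 − 0.95² = 0.0975, or 9.75%.
- Correlated (simulation, 1,000,000 draws): 9.5% at r = 0.3, 9.1% at r = 0.5, 8.4% at r = 0.7, 7.0% at r = 0.9.

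**3. Any of five instruments suffices (SIS plus the four affective scales).**
- Independent: 1 − 0.95⁵ = 0.226, or 22.6%.
- Correlated: 20.8% at r = 0.3, 18.2% at r = 0.5, 14.9% at r = 0.7, 10.1% at r = 0.9.

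Scales of one domain will be correlated, so 22.6% is an upper bound.

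**4. Both endpoints required (SIS and one affective variable).** No alpha adjustment is needed; the error rate stays at or below 5%. Power is the issue.
- If each test had the stated 80% and the tests were independent: 0.80 × 0.80 = 0.64, or 64%.
- At 50 per arm the mean of each test statistic is d√(n/2) = 0.5 × √25 = 2.5. Joint power is 0.697² ≈ 0.486 at r = 0, about 0.52 at r = 0.3 and about 0.55 at r = 0.5.

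The drop from 80% to 64% at independence is due to requiring two wins. The further drop to 49% arises because a single test at 50 per arm has about 70% power, as in step 1.

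**5. SIS alone, or SIS first in a fixed sequence.** SIS is tested at two-sided 5% and the affective test is opened only after an SIS success. The family-wise error is at most 5%, and the SIS test loses no power.

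**The case against.** A reader might infer that the trial's 5% error rate is simply not held, and that a significant result on any one of five scales would count as success. The article does not support that. It nowhere says that one win is enough, and both hypothesis statements use 'and'. Read as requiring both, that wording keeps the error rate at or below 5%. The inflation is therefore conditional. The five-test figure is more conditional still, because Statistical analysis treats affective symptomatology grammatically as one dependent variable, and the article does not say that each scale gets its own test.

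It can also be said that a testing order, an alpha split or the scoring of a composite is commonly left to a statistical analysis plan, which is not shown here. That stands: the absence of such a rule is not the point. What remains is that the article fixes the number of primaries in two incompatible ways, and no further document can make Power agree with Outcome measures.

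A third objection is that the authors had a reason for a second primary: they state that functioning is only partly explained by symptoms. That also stands. It argues for keeping affective symptomatology in the confirmatory set, but not for leaving its variable and its place in the testing undefined.

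**Conclusion.** The contradiction between one primary and two is real and lies within the protocol article. Its consequence depends on a success rule that the article does not give:

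- **Either endpoint counts:** family-wise error of about 9 to 10% for the two named endpoints (9.75% if independent, 9.1% at r = 0.5), with a ceiling of 22.6% if five instruments were tested separately and independently.
- **Both must win:** error control holds, but the stated 80% power does not. It is 64% with independent tests at 80% each, and about 49 to 55% at 50 per arm with d = 0.5 on both and r from 0 to 0.5. Part of this second range belongs to the separate sample-size shortfall.

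The correlations and the affective effect size are assumptions. The conclusion that alpha and power cannot both be as stated for two primaries does not depend on their exact values: over the correlations examined (0 to 0.9), two either-wins tests stay above 5%.

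**What to change.** By amendment before unblinding:

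1. Test the adapted SIS maladjustment score at week 14 first, at two-sided 5%, as the Power section already implies.
2. Test affective symptomatology at week 14 second, only if SIS is significant, on one named instrument or with Holm across the four.
3. Bring the abstract, the endpoint list and its rationale under Outcome measures, and the primary-analysis paragraph into line with this order.

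This holds 5% overall, costs the SIS test no power and needs no extra patients on account of multiplicity. It does not repair the separate sample-size shortfall.

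The cost is that a confirmatory affective claim depends on SIS succeeding. It is also a substantive change to a published endpoint hierarchy, not only a change of wording: the trial was recruiting, with half the patients randomised by March 2013. It remains credible if made before unblinding, since the analysing statistician is described as blinded throughout.

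The alternatives cost more. A Bonferroni split over two endpoints (0.025 each) leaves 59.0% power per test at 50 per arm and needs 78 per arm for 80%. A both-must-win rule has the joint power shown in step 4.

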Rationale for choosing the presented inclusion and exclusion criteria are as follows. First degree relatives of affected individuals have a ten-fold increased risk to also develop the disease compared to relatives of unaffected controls [35]. Twin and adoption studies have provided compelling evidence for heritable factors playing a major role in the pathogenesis of BD (see [36]). A genetically enriched population with first affective symptoms that already impact psychosocial functioning seemed to us the best way to identify subjects at high risk for developing BD. Participants must not already be diagnosed as having unipolar or bipolar affective disorders but can be diagnosed as having cyclothymia, attention deficit/hyperactivity disorder (ADHD), personality disorder or psychosis of less than seven days duration, if the symptomatology is not explained solely by this diagnosis. In view of the often unspecific presentation of high-risk subjects, this ensures reduction of false-negative recruitment, while at the same time of course the risk for false-positive enrolment is increased. The pilot findings by Bechdolf *et al*. [17,18] which indicated conversion rates to four days of mania in up to 30% within 12 months, depending on the criteria applied, support this approach of inclusion criteria definition. The diagnostic procedure comprises using the SCID plus the result of a consensus board of two clinical psychiatrists per centre.

Subjects in both treatment groups are allowed to use unstructured consultations with their usual treating physician at any time. After the intervention period, subjects in both groups are allowed to use unstructured psychotherapy sessions and psychopharmacotherapy if needed (restricted to intermittent symptomatic treatment of unspecific symptoms such as sleep disturbances and anxiety/agitation administered no longer than seven days). As mentioned, a stable antidepressant medication with SSRI, venlafaxine, duloxetine, mirtazapine or valdoxan (stable means intake for at least eight weeks) is allowed at randomisation and can be prolonged during the study. Formal, structured psychotherapy and psychopharmacotherapy other than described before results in study drop-out.

As mentioned in the inclusion criteria, written informed consent is obtained from each subject after thorough information about the study has been provided.

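### The primary week-14 ANCOVA fills missing values by LOCF, which can bias the group contrast in either direction; the repeated-measures analysis already planned would be a sounder primary

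*Protocol article*

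**What the plan says.** The Statistical analysis section of the protocol article specifies the primary efficacy analysis as an ANCOVA at week 14, run separately for SIS and for affective symptomatology. The covariates are baseline SIS, baseline affective symptomatology, centre, age, sex, education and group. The population and missing-data rule are "intention-to-treat (ITT) analysis with last observation carried forward (LOCF) in case of missing values". No other missing-data method is named. The same section says "In all cases, the 14-week value is the primary time-point of interest" and "A repeated measures analysis will be carried out as a secondary result".

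Three other statements bear on how often LOCF would be used:

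- Power section: "we assume conservatively that there will be about a 30% drop-out rate, an estimate that was accounted for in the sample size estimation". No time point is attached to the 30%.
- Power section: "Follow-up of subjects that drop out of the study will last for the planned duration of the study".
- Setting and participants: "Formal, structured psychotherapy and psychopharmacotherapy other than described before results in study drop-out".

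Table 1 (Outcome measures) places SIS and the symptom scales at baseline (week -1) and at weeks 7, 14, 24, 52 and 78. Before week 14, only the baseline and week-7 values exist to be carried forward.

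**The concern.** LOCF assumes that a subject's state at week 14 equals the state at the last visit attended, 7 or 15 weeks earlier. That sits badly with this design. Subjects qualify because functioning has fallen over the past year, so some movement back towards their usual level is to be expected in both arms. The trial's hypothesis is itself about a difference that emerges by week 14. A rule that freezes subjects part-way, or at the start, distorts the group means whenever people are changing.

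Two consequences follow. First, if more week-14 values are missing in one arm than in the other, the arms are frozen to different degrees and a difference can appear, or be hidden, for reasons unrelated to efficacy. Unequal missingness is plausible, since one arm receives structured CBT and the other receives meetings that are meant to have no therapeutic content. Second, single imputation gives filled-in scores the weight of real ones. When baseline is carried forward, the outcome is simply a copy of one of the model's own covariates, so the stated precision is not the real precision.

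**Working it through.** **The plan's own figure.** The Power section gives 50 per arm for a standardised effect of 0.5, 80% power and alpha 5%, with the sentence beginning "Sample size for the ANCOVA will be approximated with the two-sided unpaired" naming a two-sided *t*-test. With those inputs the *t*-test needs 63.8, that is 64 per arm. At 50 per arm the two-sided power is 69.7%. A one-sided 5% test gives 50 per arm. This mismatch is a separate matter. Here 69.7% serves as the complete-data reference, so that a shortfall due to sample size is not attributed to LOCF.

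**Assumptions, none of them in the protocol.** The outcome SD is 1. Change over the 14 weeks is linear, so half of it has occurred by week 7. Every subject counted as missing has no week-14 value. There are 50 per arm, so the standard error of the difference is √(2/50) = 0.20 SD.

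**A. No true effect, unequal missingness (20% versus 40%, mean 30%), both arms improve by 0.5 SD.** Expected mean change in an arm with missing fraction p is (1 − p) × 0.5 + p × v, where v is the carried-forward change.

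- Week 7 carried (v = 0.25): 0.8 × 0.5 + 0.2 × 0.25 = 0.45, against 0.6 × 0.5 + 0.4 × 0.25 = 0.40. Spurious difference 0.05 SD, or 0.05/0.20 = 0.25 standard errors. P(|N(0.25, 1)| > 1.96) ≈ 5.7%.
- Baseline carried (v = 0): 0.40 against 0.30. Spurious difference 0.10 SD, or 0.5 standard errors. P(|N(0.5, 1)| > 1.96) ≈ 7.9%.

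Swapping the arms reverses the sign. A common improvement of 0.8 SD with baseline carried gives 0.8 × 0.2 = 0.16 SD and 12.6%. Missingness of 10% versus 20% with 0.5 SD improvement and baseline carried gives 0.5 × 0.1 = 0.05 SD. These error rates use the unadjusted standard error. The ANCOVA's standard error is smaller when baseline predicts outcome, so the same bias would weigh somewhat more there.

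**B. True effect 0.5, equal 30% missing, and drop-outs would also have had the full effect.**

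- Week 7 carried: 0.7 × 0.5 + 0.3 × 0.25 = 0.425; two-sided power at 50 per arm about 56%.
- Baseline carried: 0.7 × 0.5 = 0.35; power about 41%.

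The complete-data reference is 69.7%. Simply losing 30% (35 per arm, full effect of 0.5) would give 54.1%.

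**The case against.** The strongest reply is that LOCF may have little to do. The rule operates only on missing values, the protocol commits to following drop-outs, and a week-14 score obtained from such a subject is not missing. A reader might infer from the two statements together that real week-14 outcomes would be overwritten by earlier ones. The text does not support that: nothing says that data after drop-out are discarded, and following drop-outs reduces the use of LOCF. At most, the article does not say in so many words that those data enter the primary ANCOVA, which is a clarification the full plan may already contain.

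A reader might also infer that drop-out is driven by deterioration, because starting non-permitted treatment counts as drop-out. The rule concerns treatment received, and deterioration is an inference. It also follows text on what is allowed once the intervention period is over, so it is not shown to act mainly before week 14. The argument here does not rest on it.

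Three further points stand. The 30% has no time point, is described as conservative, and belongs to a study that runs to week 78, so the share missing at week 14 may be well below it. Most of the gap between 80% and the power figures in B comes from the sample size or from losing data at all: 56% with week 7 carried is close to the 54.1% left by simple loss. And the 0.35 and 0.425 assume that non-completers would have gained the full benefit; under ITT, some attenuation in them is real.

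These points limit the size of the problem. They do not make LOCF a good stated primary rule for whatever is missing at week 14.

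**Conclusion.** The point holds as a criticism of a stated choice: LOCF is a weak primary method here and should be changed, although the trial is not shown to be invalid with it. If missingness at week 14 differs by arm while both arms are changing, the primary contrast is biased, and the sign depends on which arm loses more. Under the assumptions in A, the size is 0.05 to 0.10 SD, with type I error of about 5.7% to 7.9%. Under those in B, the estimate falls from 0.5 to between about 0.43 and 0.35, and power from 69.7% to between about 56% and 41%. Within each range the larger distortion requires every missing subject to have no week-7 visit. Both ranges put the full assumed drop-out at week 14 with no follow-up value, so they are upper-end for the missing share. They are not a bound, because a larger common improvement would raise the bias in A. To the extent that drop-outs attend week 14, the imputation bias does not arise.

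**What to change.** 1. Make the repeated-measures analysis primary, as a likelihood-based mixed model with treatment, visit and treatment-by-visit terms and the planned covariates, and use the week-14 group contrast as the test.
2. Include the baseline score as a response rather than only as a covariate, or use multiple imputation. With baseline only as a covariate, a model of weeks 7 and 14 would omit subjects who have no visit after baseline, and these are the subjects for whom LOCF does most damage.
3. State that week-14 values from subjects who leave the intervention or start other treatment enter the primary analysis as observed.
4. Keep LOCF as a sensitivity analysis.

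The cost is analysis wording and modest programming. No visits are added, because follow-up of drop-outs is already planned. The downside is reliance on a missing-at-random assumption, which the data cannot confirm. The model also does not restore information that was never collected, so obtaining week-14 data from drop-outs remains the main protection. The change should be fixed before unblinding.
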